### 5.1.3. Interim Analysis

A blinded primary end-point interim analysis will be conducted by LO at months 12 and 24 after the study opens. The DSMB will determine a priori stopping rules for efficacy and/or occurrence of serious events (the latter is described under Safety Monitoring, section 5.2.3). For efficacy endpoint, if the stopping rule is reached the DSMB will be presented with unblinded results (i.e. they will be able to ascertain which results correspond to the intervention arm). Based on these results, the DSMB will present recommendations to the Steering Committee regarding early stopping or continuation of the trial. Given the minimal risk involved, the modest benefit anticipated, and characteristics of the intervention, which make it unlikely for there to be a concurrent breakthrough result from another study, no changes in the course of this study are expected.

## 5.2. Potential Risks and Benefits

As a result of participating in the study, we anticipate that enrolled subjects (patient and parent) or participating providers will be exposed to the following risks and benefits:

### 5.2.1. Potential Risks for Enrolled Subjects (Patients and/or Parents)

*Burden from answering study surveys:* Expected to be minimal. PQ weekly surveys take on average 10 minutes to be completed and parental surveys between 15 and 30 minutes (for monthly and baseline surveys respectively). Parents can choose to answer monthly parent surveys online or using another method of their preference (phone or in-person). PQ Surveys have been administered already over 1200 times. Only three minor adverse events have been reported (during our pilot) related to the malfunction of the web system which resulted in parents receiving repeated emails. The system was immediately brought down until the glitch was repaired. None of the episodes resulted in a subject withdrawing from the study, and were reported as acceptable burden and understood as part of what the pilot entailed. Also, these malfunctions lead to a permanent safeguard build in the system that blocks the delivery of multiple emails. No further events were reported after this safeguard was implemented. Participants may also be slightly inconvenienced by the exit interviews. We will schedule them at their convenience.

There is a minor risk of emotional reactions such as sadness, anxiety, depression, and fear as a result of completing any surveys or interviews. Notably, no significant psychological adverse events were reported during the pilot. Should a patient or parent become upset as a result of completing online study instruments, face-to-face or phone interviews, they may stop answering. If at any time, the RC finds that a parent or patient appears upset by study procedures, they will notify the local PI who will contact the participant within 24 hours to follow-up. If deemed necessary, the local PI may suggest to the parent or patient that s/he contact their psychosocial provider or, if they have not been in contact with one, the PI can arrange a consultation with someone from the Pediatric Psychosocial Oncology Program.

*Risk resulting from randomization:* As a result of randomization, subjects may not receive the most efficacious treatment. For example, not being exposed to the Response intervention (control arm) may result in patients having persistent distress, however given that these patients receive usual care, it is expected that if persistent distress is identified it will be addressed by primary oncology teams as usual. On the other hand, being exposed to the Response intervention may result in side effects related to medications or complementary therapies recommended for symptom management, that may not have otherwise been prescribed; however, all participating PC teams include Hospice and Palliative Medicine board certified physicians who have extensive experience with symptom management. Furthermore, Response Team recommendations will be funneled through the primary oncology team. *None of the risks are above and beyond what a patient receiving cancer care might experience anyway.*

*Potential for Confidentiality breach:* Because of the safeguards in place, we believe that subjects' confidentiality will not be affected and the risk of serious breaches is extremely low. See Section 6.3 for a description of the data protection procedures in place.

### 5.2.2. Potential Risks for Health Care Providers

An additional potential burden of this study is the time commitment of staff providers. Primary oncology teams will be contacted to identify patients, and some will participate in an in-depth interview (about 20 minutes long). For those having patients in the intervention arm, the integration with the Response team may slightly increase the time dedicated to the patient because of reading, answering emails, or needing to contact or monitor a patient in distress. This burden is expected to be similar to what is typical for when a patient participates in a cancer-directed therapy clinical trial. Also, given that we will typically conduct less than one interview per provider and the relatively small numbers of subjects at each site at any given time (maximum of 5), it is unlikely the burden will fall on any single provider. On the other hand, palliative care (Response) team providers will increase their workload somewhat. They will consult on subjects who may not have been consulted otherwise, which implies time for the visit, writing notes and other coordination activities that may result from the consult. Palliative care teams rotate their on-call providers frequently, so this extra burden will be distributed across providers. Further, as early integration is a goal that most palliative care teams aspire to, the study is seen as an acceptable burden as it may help teams understand staffing needs, should PQ Response result in a positive effect. We will make every effort to conduct provider interviews at times that are convenient for them and minimize staff burden in general.

### 5.2.3. Safety Monitoring

Safety monitoring will be the responsibility of the SDC and the DSMB. Information on all potential types of adverse events will be collected at all assessment points and recorded on standard forms. In preparation for their quarterly feedback, the DSMB will analyze the rates of adverse events and evaluate the possibility that the intervention is causing harm. If at any point the stopping rules for adverse events are reached (such as a death, suicide or serious consideration of suicide, or a change in mental health requiring hospitalization, that is felt to be related to a recommendation of the Response team), we will suspend study activities and try to determine if there is any link between study procedures and the adverse event and determine if any modification is advised or if the study should be stopped. If an adverse event is detected, the PI will be responsible for promptly reporting it consistent with Dana-Farber Harvard Cancer Center, local sites, and funding agency policies.

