| Trial Coordinating Unit | [name]
[name]
[name]
Project Manager
[name] | 
Study planning
           Generation of study materials (for participants, training, and PediQUEST web)
           Development and maintenance of PediQUEST web
           Responsible for trial master file
           Assist sites with ethics committee continuing reviews and protocol amendments
 Adverse events and protocol violation reporting to IRBs
           Budget administration and contractual issues with individual centers
           Organization of SC, SDC, DSMB, and biweekly study meetings
           Acts as the Study Data Coordinating Center
 
 
• Develop study SOPs
 
• Provide data management plan
 
• Audit data quality and trial progress reports and provide feedback and advice to local PIs
 
• Send reports to DSMB and SC
 
• Data verification
 
• Transcription of audio files
 
• Maintenance of trial IT system and data entry
 
 |
| Local Research Units           | Local PIs (see members above)
Site Research Coordinators (RCs)                            | 
Local PIs will oversee the site's investigation activities and liaise with PI
           Participate in SC and SC's quarterly meetings
           Assist with coordination of training at the sites
           Participate in study promotion activities
           Participate in listserv activities
           Report any adverse event or protocol violation to the SDC and PI
 RCs will be responsible for identification, recruitment, data collection and completion of CRFs, along with follow up of study patients and adherence to study protocol and investigator SOPs
                                                                                                                                                                                                                                                                                                                                                                                            |

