management skills (especially non-pharmacological strategies). Response teams are expected to maintain fluid and direct communication with the primary oncology team (P.O.T.) via email, phone or face-to-face to discuss their findings and recommendations. Ultimately, the P.O.T. will hold the decision to implement recommendations. Whenever recommendations are made (by P.O.T. or Response team) a designated member of the Response team will follow-up with the family to assess results and make further recommendations/contact P.O.T. as necessary. In the event that after following the proposed plan, there is a lack of adequate response (increase or no change in symptom scores or indication by patient or parent that relief is not sufficient), Response teams are encouraged to meet with local PIs to discuss the case. In addition, the confidential PediQUEST listserv will be available for use by Response team members (see below in Support). All communications and visits will be documented in charts. Once the proposed follow-up is completed, participants in the intervention arm will be offered the opportunity to continue being followed by the PC team (it will be clearly explained that use of PediQUEST web will be discontinued at this point).

At each site, research staff and the Response team will complete a schema to identify Response team members in charge of different aspects of the intervention. Specifically, the schema will indicate who will be alerted about new participants, who will receive the notice to schedule an initial visit, who will be responsible for initiating conversations with the P.O.T., who will receive PQ reports and distribute them to other team members, and who will be in charge of patient follow-up when recommendations are made. We expect that there will be two people in direct contact with the RC, one with a stronger administrative role and one with a clinical role (Figure 7). However, team members can be responsible for one or more tasks, structure may vary according to the organization of PC teams, and should be regularly revised to accommodate team rotation or other changes.

[figure not shown]

**Figure 7. Early Integration of the Response Team Activities.** Main activities of early integration component are depicted in the figure.  

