*References:* RC: Research coordinator; RT: Response Teams; P.O.T.: Primary Oncology Team; PQ e-PROMS: PediQUEST electronic patient reported outcome measures; Local PI: Site Principal investigator; PQ Listserv: PediQUEST Listserv (expert listserv).

*Support for Response Team: Training and Expert Consult.* Response teams will receive a 48-hour online refresher course covering symptom management strategies. We will use material from the Education in Palliative and End-of-life Care for Pediatrics curriculum (EPEC-Pediatrics) developed by Co-I [name] and PI [name]. Twelve online EPEC-Pediatrics modules with structured, brief evaluation covering prevalent physical and psychological symptoms will be accessible over the data collection period. Online training will be complemented with a 1-day site-based training that will cover study procedures, team work, and family activation strategies (See Appendix-Intervention Materials, for training agenda). Per the EPEC Pediatrics curriculum, case-discussion and role-play techniques will be used during the face-to-face training to evaluate skill acquisition. Study investigators [name], [name], [name], [name], who are all EPEC-Pediatrics Master Facilitators, will be responsible for the face-to-face training. In addition, regular meetings of the active Response team members with local PIs are strongly encouraged. The goal of these meetings is to maintain open discussion about the active cases and ensure that therapeutic plans are updated. In addition, a PQ Response listserv including an interdisciplinary roster of national PC experts (see Appendix-Intervention Materials, for expert's roster) will be available to all Response team members and could be used at any point in the care of a study participant. Of note, listserv members will be instructed to comply at all times with HIPAA's privacy and security rules when exchanging patient information. PQ Response listserv member guideline will follow the American Academy of Pediatrics Pediatric Hospice and Palliative Medicine (PHPM) LISTSERV® posting guidelines and the American Academy of Hospice and Palliative Medicine "Connect" Access Agreement.

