|                                             | No. consults to Listserv /No. episodes of persistent distress/month                                                                                                                                                           | PQ Reports + Listserv logs | Monthly | >80%   |

Abbreviations: MR: Medical record; RT: Response Team.

\*The Study Data Center will provide a set of smart text phrases to facilitate the documentation of intervention processes of local Response teams on the medical record. All palliative care notes from patients in the intervention arm will be abstracted and saved as pdf. Indicators will be built using pdfs.

Qualitative fidelity evaluation: All patients and parents, and a convenient sample of providers will be invited to participate in exit interviews that will inform fidelity assessment (see section 2.5.3). Providers selected to do these exit interviews will receive a \$50 gift card.

To monitor intervention fidelity, site RCs will collect all palliative care notes on intervention arm participants on a monthly basis, convert them to pdf, and send them to the PM using a send secure system (or a shared secure server such as Dropbox). The PM will receive monthly reports on the number of distress episodes reported through PediQUEST, among patients in the intervention arm, collect information on the use of listserv, and communicate with local PIs on an as needed basis to clarify information. With this information, the PM and VD (co-I) will build the indicators

and send monthly progress reports to the DSMB and SC (see section 5.1.2). Reports will be analyzed by the Data and Safety Monitoring Board to detect patterns of non-adherence or protocol deviations. If deviations in intervention processes are detected, they will be discussed with the local PI to decide whether retraining or site visits are indicated.

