### 2.5.2. Medical Record Abstraction

The following variables will be abstracted from the medical records at week -2 (study entry): child diagnosis, cancer-directed treatments, and symptom treatments.

From week 0 to 16 (i.e. randomization point to end of follow-up), information will be abstracted every four weeks by RCs summarizing events that occurred in the four-week window including: disease status (stable, progression, remission), date of change in status when appropriate, cancer-directed and symptom treatments, formal PC referrals, hospitalizations, No. of psychosocial clinician encounters and No. of PC encounters documented. Chart abstraction forms will be entered into PediQUEST web.

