## 4. Methods: Data collection, management, and analysis

### 4.1. Data collection methods

Research material for this study primarily involve patient reported outcomes and parent reports collected and stored electronically through the PQ web system. In addition, RCs will collect data for tracking purposes (with electronic (REDCap) and/or paper and pencil checklists and personal notes), do the medical record abstraction (online), and conduct the semi-structured exit interviews. Data collection protocols are identical for both arms and were described in section 2.5, participant timeline, together with instrument's psychometric properties. A sample of study instruments is presented in the Appendix.

REDCap is a web-based application that allows for the creation and management of online databases. We will run the study's enrollment tracking system and randomization module on this platform. PQ web is a web-based application that allows for the use of PROMs, includes scheduling, reminder, and scoring and feedback capabilities. The PQ Response's Baseline Packet, PQ-Surveys, Monthly Parent Surveys, and the Medical Record Abstraction will be collected through this system. Participants can use the PQ mobile application to answer surveys and view reports; providers can also download the App and use it to view patient reports. Both systems can handle multicenter studies and easy transfer to common statistical packages. The semi-structured exit interviews will be conducted face-to-face or over the phone and audio-recorded.

All participating sites will designate an RC who will be trained in all study procedures (9 hours including role play), participate in monthly meetings, generate reports of research activities, prepare and maintain IRB documentation, enroll participants, and be in charge of the communication with oncologists and Response teams regarding subjects' participation. Strategies to enhance retention have been described in section 2.3.2, adherence.

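### The adverse-event comparison is at risk of detection bias: no common adverse-event item is listed, and extra channels to the people who report events exist in the intervention arm only

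*Protocol*

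**What the plan says.** Section 5.2.3 sets the purpose: before each quarterly report, "the DSMB will analyze the rates of adverse events and evaluate the possibility that the intervention is causing harm". On collection, the same section says: "Information on all potential types of adverse events will be collected at all assessment points and recorded on standard forms". Section 4.1 adds: "Data collection protocols are identical for both arms and were described in section 2.5". On its face, then, collection is the same in both arms.

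The shared schedule in section 2.5 consists of weekly PediQUEST surveys, monthly parent questionnaires and chart abstraction every four weeks. The abstraction list in section 2.5.2 covers disease status, cancer-directed and symptom treatments, and "formal PC referrals, hospitalizations, No. of psychosocial clinician encounters and No. of PC encounters documented".

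Three further contacts apply to intervention children only:
- Section 2.3.1.1: after a recommendation, "a designated member of the Response team will follow-up with the family to assess results".
- Section 2.3.1.1, on support for the Response team: "regular meetings of the active Response team members with local PIs are strongly encouraged".
- Section 2.3.2, for fidelity monitoring: "site RCs will collect all palliative care notes on intervention arm participants on a monthly basis".

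The table under Study administration structure gives local PIs the duty to "Report any adverse event or protocol violation to the SDC and PI" and has the research coordinators compile events for the PI. Section 3.2 states that research staff and clinicians are unblinded after randomization.

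**The concern.** Event rates show harm only if both arms are searched about equally hard. Here the common search is promised but has no visible content, while the people responsible for reporting learn more about intervention children than about controls. The harm that section 5.2.1 foresees is side effects of medications or complementary therapies recommended for symptoms. Such events are found mainly by asking the family or reading clinical notes, which is what the extra contacts do.

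Two errors are possible. With equal true rates, the intervention arm could show a spurious excess. Or a real excess could be dismissed as the result of closer observation. Section 5.1.1 keeps the DSMB's data blinded apart from interim results. If events are shown under masked arm labels, the members cannot tell which arm was searched harder and cannot allow for it.

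**Working it through.** The protocol states no adverse-event rate or detection rate, so there is no figure to reproduce. The check traces the routes by arm and then gives an illustration of scale.

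**Step 1: routes by arm**

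| Route | Intervention | Control | Adverse-event item listed? |
|---|---|---|---|
| Weekly surveys, monthly questionnaires (Table 3) | yes | yes | no |
| Four-weekly abstraction (2.5.2) | yes | yes | no; hospitalizations are listed |
| Coordinator contact after a missed survey (2.3.2), PI follow-up of an upset participant (5.2.1) | yes | yes | not stated |
| Routine oncology care (2.3.1.2) | yes | yes | not stated |
| Response-team follow-up (2.3.1.1) | yes | no | not named as a source |
| Response-team meetings with the local PI (2.3.1.1) | yes | no | not named as a source |
| Monthly collection of palliative care notes (2.3.2) | yes | no, even if referred | not named as a source; purpose is fidelity |

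The last three rows reach the local PI or the coordinator, who must report any event they learn of. Table 2 sets targets of a visit within three weeks in more than 90% of intervention children and contact after more than 80% of distress episodes. Controls do not meet the Response team, and their survey answers generate no report. The targets measure contact, not detection of events, so they show the direction of the imbalance but not its size.

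**Step 2: apparent rate ratio (assumed share)**

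Let s be the share of events visible only through the intervention-only channels, with equal true rates. The apparent ratio is 1/(1 − s):
- s = 0.10: 1/0.90 = 1.11
- s = 0.20: 1/0.80 = 1.25
- s = 0.30: 1/0.70 = 1.43
- s = 0.40: 1/0.60 = 1.67

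**Step 3: chance of a false signal (assumed rates)**

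Take 75 children per arm, the number randomized in section 2.6. Assume the same true risk p in both arms, from 10% to 40%, with detection of 90% in the intervention arm and d in controls. The observed risks are a = 0.9p and b = d·p, so the apparent risk ratio is 0.9/d.

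The chance of a significant excess in the intervention arm at two-sided 0.05 is Φ[(a − b − 1.96·SE0)/SE1]. SE0 uses the pooled risk and SE1 the separate risks. Example with p = 0.20 and d = 0.70: a = 0.18, b = 0.14, SE0 = 0.0599, SE1 = 0.0598, and (0.04 − 0.1173)/0.0598 = −1.29, so Φ = 0.098.

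| Control detection d | Risk ratio | Chance of a false excess, p from 10% to 40% |
|---|---|---|
| 90% | 1.00 | 2.5% |
| 80% | 1.13 | 4% to 7% |
| 70% | 1.29 | 7% to 18% |
| 50% | 1.80 | 16% to 59% |

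A small detection gap does little; a large one matters. The protocol gives no basis for choosing between them. It also specifies no formal test, so the last column conveys scale only.

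**The case against.** A reader might infer that adverse events come to light in the intervention arm only, or that the harm comparison is biased or uninterpretable. The documents do not support either. Sections 5.2.3 and 4.1 promise collection that does not depend on arm, on standard forms. Those forms, the appendices and the operating procedures are not at hand and may contain an adverse-event query. The abstraction list is introduced as a list of inclusions and need not be complete. No section names the three intervention-only contacts as adverse-event sources, and the team's meetings with families and with local PIs are encouraged rather than required. Controls are far from unobserved: they receive routine oncology care, their charts are abstracted on the same schedule, and coordinators contact families in both arms.

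The effect on decisions is also limited. The stopping examples in section 5.2.3 turn on whether an event is judged related to a Response-team recommendation, not on a ratio between arms. Reports under section 5.1.2 are produced overall and by site. Extra contact is inherent in an unblinded trial of integrated care.

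Most of this stands, and it limits the point to a risk of unknown size. It does not remove the point. Whatever the standard forms contain, the protocol has no rule that separates events found on the common schedule from events learned through intervention-only contact. The same unblinded staff report both.

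**Conclusion.** The concern holds as a risk of detection bias in the between-arm comparison of events that do not lead to hospitalization, probably towards more events in the intervention arm. It rests on three documented facts: event rates are used to judge harm; no adverse-event item appears in the listed instruments or abstraction fields; and the unblinded people who report events have additional information on one arm. Deaths and hospitalizations are little affected, although whether a death is attributed to the intervention remains a matter of judgment.

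The size cannot be derived from the protocol. Ratios of 1.11 to 1.67 follow from assumed shares of 10% to 40%; with equal detection there is no bias. A comparison confined to events from common scheduled sources would remain interpretable. The change is worth making because it is cheap and concerns how data are collected, which an analysis plan cannot repair afterwards.

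**What to change.** 1. Add the same adverse-event and side-effect field to the four-weekly abstraction for every randomized child. If wanted, add the same question to the monthly parent questionnaire in both arms.
2. Retrieve palliative care notes for controls who are referred, on the same terms as for intervention children.
3. Record the source of every event: common schedule, Response-team contact, PI meeting, fidelity review or other.
4. Continue to report and act on all events. Show the DSMB both the all-source rates and the rates from common scheduled sources, with the latter as the like-for-like comparison. List events found only through Response-team contact or fidelity review separately.

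Events known only through the Response team should not be removed from the safety record. Dropping them while counting events from control notes could reverse the bias and hide the side effects anticipated in section 5.2.1.

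The cost is slightly longer abstraction, note retrieval for referred controls and one extra column in the safety table. No additional visits are needed, and the field can be completed from charts for children already randomized. Some imbalance will remain, because intervention charts hold more notes.
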